## Abstract

**Background::**

The forms of treatment which are available for these patients include internal fixation, hemiarthroplasty (HA), or total hip arthroplasty (THA). Both HA and THA are widely used methods of hip replacement after displaced femoral neck fracture (DFNF). Our purpose is to analyze the long-term outcomes of these 2 different forms of treatment, which are suitable for active patients with femoral neck intracapsular fractures ≥80 years of age without advanced osteoarthritis or rheumatoid arthritis.

**Methods::**

This study is designed as a single-center randomized controlled trial. The participants will be randomly assigned to either the THA group or the HA group. Information will be collected from all participants after obtaining written informed consent in accordance with the Declaration of Helsinki and ethical board approval. Inclusion criteria include: displaced intracapsular femoral neck fracture, capability to obtain informed consent, no known metastatic disease, no contraindications to anesthesia, age ≥80 years, and ability to understand written Chinese. Patients will be evaluated at 3 months, 6 months, 1 year, and 3 years after surgery. At the time of the final follow-up, patients were assessed with use of the Harris hip score (HHS) and walking distance. Secondary outcomes of interest include postoperative complications, including 90-day medical complications (acute myocardial infarction, deep vein thrombosis, pulmonary embolism, intestinal obstruction, renal failure, and pneumonia) and surgical complications within 1 year (dislocation, infection, and revision replacement).

**Results::**

This trial is expected to be the largest randomized trial assessing the efficacy of THA and HA and powered to detect a potential difference in the primary outcome.

**Trial registration::**

This study protocol has been registered in Research Registry (researchregistry6203).

## Introduction

1

With the aging of the world population, the proportion of elderly people is increasing, leading to an increase in the incidence of osteoporotic hip fractures.^[1]^ It is estimated that about 1.6 million hip fractures occurred in 2000, and by 2050, the incidence of hip fractures worldwide is expected to increase to >6 million.^[2–4]^ About half of hip fractures have displaced femoral neck fracture (DFNF, garden type III or IV), which may lead to nonunion or no vascular necrosis.^[5]^

The forms of treatment which are available for these patients include internal fixation, hemiarthroplasty (HA), or total hip arthroplasty (THA). Both HA and THA are widely used methods of hip replacement after DFNF. HA is a less complicated operation and is associated with lower dislocation rate, lower blood loss, and lower initial cost. However, due to complications such as acetabular erosion, some patients receiving HA treatment need to be converted to THA.^[1,6–10]^ On the other hand, THA can increase patient satisfaction and improve postoperative function. In recent years, it has been increasingly used to treat DFNF, especially in young and active emergency patients.^[11–15]^

The long-term prognosis of elderly patients (over 80 years of age) with DFNF treated with HA or THA is unclear. Several studies with a follow-up of >5 years have been published.^[16–19]^ However, the number of randomized controlled trials is small. Therefore, the treatment of these patients is still controversial, and a well conducted randomized controlled trial with large sample sizes is required. Our purpose is to analyze the long-term outcomes of these 2 different forms of treatment, which are suitable for active patients with femoral neck intracapsular fractures ≥80 years of age without advanced osteoarthritis or rheumatoid arthritis.

## Material and method

2

### Trial design and ethics

2.1

This study is designed as a single-center randomized controlled trial. The participants will be randomly assigned to either the THA group or the HA group. Our study protocol has been approved by the local ethics committee of the Fourth People's Hospital of Jinan Research Ethics Committee (B201010343) and has been registered in Research Registry (registration number: researchregistry6203). Information will be collected from all participants after obtaining written informed consent in accordance with the Declaration of Helsinki and ethical board approval.

### Randomization and blinding

2.2

An author will provide a set of 280 random numbers for the allocation sequence using a website (http://www.randomization.com). The random allocation sequence will be available to this author only and thus it will be concealed from the other research team members. The included participants will be randomly assigned to either the THA group or the HA group in a ratio of 1:1. The surgeons, anesthesiologists, and nurses providing intra- and postoperative care, as well as the research coordinator assessing outcomes, are all kept blinded to allocation results.

### Eligibility criteria

2.3

Inclusion criteria include: displaced intracapsular femoral neck fracture, capability to obtain informed consent, no known metastatic disease, no contraindications to anesthesia, age ≥80 years, and ability to understand written Chinese. The exclusion criteria are: failure to meet the inclusion criteria, including refusal of consent, radioactive osteoarthritis of hip fracture or rheumatoid arthritis; suspected pathological fractures; patients who are bedridden or could barely move to a chair; Alzheimer disease.

### Treatment and control groups

2.4

A cemented collarless polished tapered (CPT; Zimmer, Warsaw, Indiana) femoral component is implanted in all patients via a transgluteal lateral approach. The THAs are implanted with a 28 mm cobalt chrome femoral head articulating with an all-polyethylene cemented acetabular component without a long posterior wall (ZCA; Zimmer). The HA group receives an appropriate size standard deviation femoral head internal fixator (Zimmer). The size of the head is measured from the hemispherical template during surgery and is available in 2 mm increments. Postoperatively, patients are mobilized with full weight-bearing on the second postoperative day and graduate from a walker to a cane prior to discharge.

### Outcome measurements

2.5

Patients will be evaluated at 3 months, 6 months, 1 year, and 3 years after surgery. At the time of the final follow-up, patients were assessed with use of the Harris hip score (HHS) and walking distance. The walking distance at the time of the final follow-up is reported by the patients themselves. Anteroposterior and lateral radiographs of the involved hip are made. Secondary outcomes of interest include postoperative complications, including 90-day medical complications (acute myocardial infarction, deep vein thrombosis, pulmonary embolism, intestinal obstruction, renal failure, and pneumonia) and surgical complications within 1 year (dislocation, infection, and revision replacement).

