### Statistical analysis

2.7

All data will be entered into STATA software (StataCorp; Texas, USA) by 3 investigators for statistical analysis and calculation. The accuracy of these data is analyzed by 2 other researchers. According to its distribution, the Mann–Whitney *U* test or Student *t* test is used to test the statistically significant differences between the treatment groups of HHS and other continuous parameters. Chi-square test or Fisher exact test is used to analyze dichotomous variables, such as revision and dislocation rates. All analyses are 2-sided analyses, and a *P* value of <.05 is considered statistically significant.

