## Discussion

3

With the increase in the elderly population, the occurrence of femoral neck fractures becomes more and more common, which adds socio-economic significance to these fractures. Successful management is essential for each patient and the future demand for medical services. The goal of any treatment for femoral neck fractures is to restore the patient to a satisfactory functional state as quickly as possible, while minimizing morbidity and mortality, and minimizing the need for reoperation. There is ongoing debate about the comparative benefits of hemiarthroplasty and THR for patients (older than 80 years) an acute DFNF. Our purpose is to analyze the long-term outcomes of these 2 different forms of treatment, which are suitable for active patients with femoral neck intracapsular fractures ≥80 years of age without advanced osteoarthritis or rheumatoid arthritis. This trial is expected to be the largest randomized trial assessing the efficacy of THA and HA and powered to detect a potential difference in the primary outcome.

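### As written, no pre-fracture function enters the analysis: a minor, cheaply repaired loss of precision, of recovery reporting and of a check on the survivors

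*Protocol article*

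**What the plan says.** Section 2.5 (Outcome measurements) of the protocol article gives the schedule: "Patients will be evaluated at 3 months, 6 months, 1 year, and 3 years after surgery". Function is placed at the end of it: "At the time of the final follow-up, patients were assessed with use of the Harris hip score (HHS) and walking distance". On walking distance it adds: "The walking distance at the time of the final follow-up is reported by the patients themselves".

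The only entry information on mobility is an exclusion in section 2.3 (Eligibility criteria), which removes "patients who are bedridden or could barely move to a chair". No section names a pre-fracture walking distance, walking aid or functional score.

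Section 2.7 (Statistical analysis) names the tests. Depending on the distribution, a Mann-Whitney U test or a "Student *t* test is used to test the statistically significant differences between the treatment groups of HHS and other continuous parameters". Neither has a baseline term.

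The trial's objective is stated in the Introduction: "Our purpose is to analyze the long-term outcomes of these 2 different forms of treatment". It is directed at active patients aged 80 or over.

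**The concern.** Patients who pass the mobility exclusion can differ widely. One may have walked only indoors and another several kilometres. If both report 200 m at the end, that is full recovery for the first and a large loss for the second, yet the listed outcomes and tests treat them alike.

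Three things depend on a pre-fracture value:

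- **Precision.** Differences in walking ability that existed before the injury stay in the error term of an unadjusted test.
- **Interpretation.** Return to a patient's own earlier walking level cannot be reported, and readers cannot judge how active the enrolled patients were.
- **Comparability of those measured.** Randomization balances the 280 patients allocated, but final HHS and walking distance exist only for survivors. If deaths differ between arms in number or kind, the survivors may differ in pre-injury function, and nothing listed would show it.

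Timing matters. A value asked for at the final visit would come from survivors only, who by then know their own result.

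**Working it through.** **1. The plan's own sample size (section 2.6).** Inputs: difference 10 HHS points, SD 20, alpha 0.05 (two-sided, section 2.7), power 90%, stated requirement 83 per group.

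- n per group = 2 × [SD × (z₀.₉₇₅ + z₀.₉₀) / difference]² = 2 × [20 × (1.960 + 1.282) / 10]² = 84.06, so 85. The t-based figure is 85.03. The stated 83 is within two patients, and power at 83 is 0.896.
- With 41% mortality: 83 / (1 − 0.41) = 140.7, so 141 against the stated 140.
- Evaluable per group: 140 × 0.59 = 82.6, about 165 of 280 in all. Power is about 0.895.

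The figures reproduce, none uses a baseline value, and the planned HHS comparison does not need one to be valid. Section 2.6 introduces mortality on a 5-year basis while the last listed visit is at 3 years, so 82.6 is the plan's sizing figure and not a forecast for 3 years.

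**2. Precision forgone on walking distance.** The documents give no correlation r between pre-fracture and final walking distance; 0.3 to 0.6 is assumed. Linear adjustment leaves a fraction 1 − r² of the variance, so the equivalent gain in evaluable patients is 1/(1 − r²) − 1.

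- r = 0.3: r² = 0.09, gain = 1/0.91 − 1 = 0.10.
- r = 0.6: r² = 0.36, gain = 1/0.64 − 1 = 0.56.

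This applies to a linear model of a continuous outcome. It does not carry over exactly to an ordinal or rank-based analysis.

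**3. The same idea applied to HHS.** The residual SD becomes 20 × √(1 − r²), with r again assumed.

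| r with final HHS | n per group for 90% power | power at 82.6 per group |
|---|---|---|
| 0 | 85 | 0.895 |
| 0.2 | 81 | 0.907 |
| 0.3 | 77 | 0.920 |
| 0.5 | 64 | 0.960 |
| 0.7 | 43 | 0.994 |

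**4. Chance imbalance among those measured.** The standard error of the between-arm difference in a standardized baseline is √(2/82.6) = 0.156 SD, so its 95% limit is 1.96 × 0.156 = 0.305 SD. An imbalance of that size moves the unadjusted HHS difference by r × 20 × 0.305:

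- r = 0.3: 1.8 points
- r = 0.5: 3.0 points
- r = 0.7: 4.3 points

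The target difference is 10 points. These shifts are already within the random error that the test allows for; adjustment would remove them. Imbalance from differential death would come on top and cannot be sized from the document.

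**The case against.** The strongest objection is that this is a condensed article. The sentence on visits is a follow-up schedule, not a list of everything recorded, and baseline data are commonly left to the full protocol or case report form. That stands as far as data collection goes: it cannot be asserted that no pre-fracture value is taken, only that none is listed. It does not dispose of the analysis, because section 2.7 does name the tests, and they are unadjusted even if a baseline value is collected.

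The second objection is that 1:1 randomization balances pre-injury mobility in expectation, so the between-arm comparison answers the trial's question without a baseline. This also stands for the patients allocated. It covers less well the survivors in whom function is measured, which is where a pre-allocation value would serve as a check.

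Two stronger readings are tempting, and the document supports neither:

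- A reader might infer that the trial cannot tell whether either implant restored function, the goal it sets for treatment. The Discussion says: "The goal of any treatment for femoral neck fractures is to restore the patient to a satisfactory functional state as quickly as possible". That describes an absolute level, which final HHS can address, not a return to the patient's own earlier state. It is also a general remark on treating these fractures, not a trial endpoint.
- A reader might infer that final walking distance is mainly a reflection of pre-injury differences. Under the assumed correlations, baseline explains 9% to 36% of the variance, leaving 64% to 91% to other sources.

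**Conclusion.** The point holds as a minor one. On the text shown, all listed evaluations follow surgery and the named tests are unadjusted, so no pre-fracture function enters the analysis. The sample size reproduces to within two patients, and the randomized comparison of final HHS is valid in expectation with about 0.895 power.

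What is lost is precision, worth about 10% to 56% more evaluable patients for walking distance if the correlation is 0.3 to 0.6; the reporting of return to pre-fracture walking level; and any check on how active the patients were and whether the surviving 59% or so are comparable between arms. The precision figures rest on assumed correlations and on linear adjustment. The survivor figure rests on the plan's own 41%. Whether the full protocol already collects the value is unknown.

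**What to change.** **Section 2.5.** At the consent interview, before allocation, record the patient's usual walking distance and walking aid before the fracture. Word the distance question exactly as at the final follow-up. If the full protocol already does this, say so in one sentence.

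**Section 2.7.** Compare final walking distance and HHS between arms adjusted for that value, with a linear model, or an ordinal or rank-based model if the distribution is skewed. As a supportive result, report by arm the proportion back in their pre-fracture distance category. Tabulate the pre-fracture value by arm for all patients allocated and again for those measured at the final visit. Adjustment deals only with the part of survivor selection that this value captures, so it is a check and not a full remedy for deaths.

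**Cost.** Two questions and the matching form fields at an interview that takes place anyway, and one covariate. The drawback is some recall error in an acutely injured patient. It is non-differential because the answer precedes allocation.

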### Sample size calculation

2.6

The smallest difference in HHS considered to be clinically important is 10 points. In our patient population, the average HHS is estimated to be 70 points, and the maximum standard deviation is estimated to be 20 points. With an alpha level of 0.05 and a power of 90%, each group will require 83 patients. However, it is necessary to state that the 5-year expected mortality rate (average age of 84 years) for the study group is approximately 60%. Therefore, the required number has increased by 2.5 times, and each study group requires a total of 200 patients. An interim analysis of the mortality identified this to be only 41% in our selected patient group and accordingly the sample size is reduced to 140 patients per group.

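### Dislocation, infection and revision are counted only to 1 year, although the aim is long-term outcome and a 3-year visit is planned

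*Protocol article*

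**What the plan says.** - **Aim.** The abstract of the protocol article says "Our purpose is to analyze the long-term outcomes of these 2 different forms of treatment". The introduction and discussion repeat this.
- **Follow-up.** Section 2.5 (Outcome measurements): "Patients will be evaluated at 3 months, 6 months, 1 year, and 3 years after surgery". HHS and walking distance are taken at the final follow-up.
- **Surgical outcome.** Section 2.5 lists, as a secondary outcome, "surgical complications within 1 year (dislocation, infection, and revision replacement"). The abstract has the same 1-year limit.
- **Known drawback of HA.** Section 1 (Introduction) credits HA with fewer dislocations, then adds that "due to complications such as acetabular erosion, some patients receiving HA treatment need to be converted to THA".
- **Imaging.** Section 2.5: "Anteroposterior and lateral radiographs of the involved hip are made". No time point is given, and acetabular erosion is not listed among the outcomes.
- **Analysis.** Section 2.7 (Statistical analysis): "Chi-square test or Fisher exact test is used to analyze dichotomous variables, such as revision and dislocation rates". No other window appears there.

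**The concern.** The introduction sets up a trade-off: HA is the simpler operation with fewer dislocations, but some patients later need THA. Revision is the listed outcome that would capture that second half, and it stops counting at 1 year while patients are followed to 3. A conversion in month 18 would be known to the trial team at the 3-year visit but would not enter the defined outcome.

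This is a rule the article states, in both the abstract and section 2.5, and not a detail it leaves open. At stake is whether the trial can report revision over the same horizon as function. As written, it would report HHS at the final follow-up beside a revision rate that ends two years earlier.

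**Working it through.** **1. The plan's own figures.** The article gives no expected rate or power for revision, so there is none to reproduce. The sample size rests on HHS: "The smallest difference in HHS considered to be clinically important is 10 points", and "the maximum standard deviation is estimated to be 20 points". With two-sided alpha 0.05 and 90% power, n = 2 × (1.960 + 1.282)² × (20/10)² ≈ 84.1, rounded up to 85 per group against the stated 83. Allowing for 41% mortality, 83 / 0.59 = 140.7, so 141 against the stated 140. Both agree to within 2 patients, and neither depends on the complication window.

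**2. Calendar share outside the window.** Planned follow-up is 36 months and the counted window is 12. Uncounted: 24 / 36 = 67%.

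**3. Person-time share, allowing for deaths.** Section 2.6 expects about 60% mortality at 5 years and then reports an interim figure of 41%, most naturally for the same 5-year quantity. Assume a constant hazard h = −ln(1 − m)/5. Person-years per patient to time t are (1 − e^(−ht))/h.

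| Mortality at 5 years | h | Person-years, 0–1 | Person-years, 0–3 | Share after year 1 |
|---|---|---|---|---|
| 41% | 0.1055 | 0.949 | 2.572 | 63.1% |
| 60% | 0.1833 | 0.914 | 2.308 | 60.4% |

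If 41% is read as mortality at 3 years, h = −ln(0.59)/3 = 0.1759 and the share is 60.7%. The result barely depends on the reading.

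**4. From person-time to events.** Person-time outside the window is not the same as events lost, which depends on when revisions happen. The article does not say. Taking a Weibull cumulative hazard with shape k and ignoring deaths, the share of 3-year revisions that falls in year 1 is about (1/3)^k when events are uncommon:

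- early-weighted, k = 0.5: 58%
- constant, k = 1: 33%
- rising linearly, k = 2: 11%

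The 1-year window would thus miss between 42% and 89% of 3-year revisions. For scale, assume 3-year HA revision of 4% to 10% in 140 patients: 5.6 to 14 events, of which 1.9 to 4.7 would be counted under the constant hazard and 0.6 to 1.6 under the rising one. These rates and shapes are illustrations only.

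**The case against.** **Timing is not documented.** The introduction does not say when erosion-related conversions occur. A reader might infer that the window removes mainly late HA failures and so biases the comparison towards HA. The documents do not support that as a fact: under the early-weighted shape above, more than half of the 3-year revisions are already counted. This objection stands, so the direction of any distortion is conditional. The mismatch between window, follow-up and aim does not depend on it.

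**Long-term function is still measured.** A reader might also infer that the trial cannot answer its long-term question at all. That goes too far. HHS and walking distance are assessed at the final follow-up, HHS drives the sample size, and the gap concerns a secondary outcome. But HHS does not count conversions, and a patient successfully converted before year 3 could score well.

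**Later counting is not barred.** Secondary outcomes are introduced as a list of inclusions, section 2.7 names revision rates without a window, and recording details may sit in a fuller protocol that is not shown. So one can say only that erosion is not listed in this article, not that it goes unmeasured. This does not lift the explicit 1-year limit on revision, however, and a later count chosen afterwards would be post hoc.

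**Deaths complicate later counts.** They do. That calls for a suitable estimator and does not justify stopping at 1 year.

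**Conclusion.** The point holds as a mismatch between a stated rule and the trial's own aim and schedule. Surgical complications and revision stop at 1 year, the last visit is at 3, and nothing in the article counts a revision or HA-to-THA conversion in between. Two-thirds of the planned months lie outside the window, or about 60% to 63% of person-time under constant-hazard mortality. How many events that loses is unknown. A lean towards HA would follow only if conversions tend to occur after year 1, which the article neither states nor rules out. The change should be made, but it does not threaten the primary HHS analysis or the sample size.

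**What to change.** Replace the 1-year limit in section 2.5 and the abstract with wording such as: *Dislocation, infection and any revision, including conversion of HA to THA, will be counted from surgery to the 3-year visit and reported by arm as cumulative incidence, with death as a competing event. The 1-year figures will be reported as an early time point.* Section 2.7 should name the same horizon for revision and dislocation.

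**Cost.** No extra visit is needed and the sample size is unchanged; the additions are event dates on the form and one analysis.

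**Downside.** Late events may be under-reported among patients lost after year 1. No visit falls between 1 and 3 years, so events in patients who die in that interval also need another source, such as hospital records. Under the hazards above, survival falls from 0.900 to 0.729 (41% at 5 years) or from 0.833 to 0.577 (60%). With 140 per group, that is 140 × 0.171 ≈ 24 to 140 × 0.255 ≈ 36 deaths between the two visits in each group.

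**Optional.** Acetabular erosion could be graded from the radiographs, but this would need a scale, readers and a stated imaging time. Grading in the HA arm alone would give no comparison between arms. It is not part of the required change.
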